### Intervention description {11a}

After successful recruitment into the study, the patients will be randomized into one of two arms:

The first arm is the current standard of care accompanied with normothermia (i.e., 36.5–37.5 °C).The second arm is the xenon intervention group, where the participants will receive inhaled xenon for 24 h with an end-tidal concentration of 50 ± 2% and normothermia (i.e., 36.5–37.5 °C) and the standard of care thereafter.

The intervention arm will receive xenon administered at 50 ± 2% in oxygen for 24 h upon admission to the intensive care unit. The concentration of xenon administered will be monitored at both the inspiratory and expiratory limbs of the rebreathing circuit using a thermoconductivity analyzer, which is automatically calibrated when the delivery system is initiated. If the concentration of xenon administered drops below 45%, the system will be flushed to displace any nitrogen emerging from blood and tissues into the closed-circuit system. Flushing will be continued until a xenon concentration of at least a 50% is reached. Xenon will be administered for 24 h through the rebreathing circuit. If the patient should require surgery for any reason during the xenon inhalation treatment, the procedure will be performed under xenon anesthesia whenever feasible. Supplemental sedative, anesthetic, and pain medication are to be provided as necessary during surgery. A failure to maintain a 50% concentration of xenon in oxygen during the treatment phase is not a reason to disqualify the patient from the study. In such a case, the treatment will be continued with the safest concentration that can be administered. The end-tidal xenon concentration of 70% may not be exceeded nor can it be less than 30% (i.e., the upper safety limit and lower efficacy limit of xenon concentration).

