Since acute hydrocephalus is relatively common after aSAH, most of the recruited patients will receive an external ventricular drain. ICP monitoring will also be performed in all patients. ICP target is set to ≤ 20 mmHg; an optimal head position of 30° will be ensured. The ICP monitoring device must be in place prior to the commencement of xenon inhalation. Mechanical ventilation and adjustments will be made based on regular treatment. The inspiratory oxygen will be adjusted to maintain a partial pressure for arterial oxygen in the range of 12–20 kPa. Minute ventilation will be adjusted to maintain the partial pressure for arterial carbon dioxide in the range of 4.5–5.5. kPa. Repeated blood-gas analysis will be performed every hour during the xenon treatment, and later whenever indicated but at least every 4 h. The following hemodynamic targets are set: cerebral perfusion pressure (CPP) > 60mmHg, mean arterial pressure (MAP) > 65mmHg. Management of hemodynamics will be primarily achieved through the use of vasopressors (e.g., norepinephrine, epinephrine, dopamine, dobutamine), and antiarrhythmic medications will be administered as needed and according to local protocols. Hypertension will be treated with vasodilators.

Serum glucose-targets are set to between 5.0 and 10.0 mmol/L and hematocrit between 0.3 and 0.45. Potassium will be supplemented if the serum potassium level is < 4 mmol/L. Plasma sodium levels will be maintained above 135 mmol/l and will not be corrected if osmotic therapy for intracranial hypertension results in an elevation of plasma sodium, unless it exceeds 155 mmol/l. Normothermia of 36.5–37.5 °C will be maintained after ICU arrival. The core temperature will be managed with infusions of diclofenac and paracetamol according to clinical routine at each center.

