### Plans for collection, laboratory evaluation, and storage of biological specimens for genetic or molecular analysis in this trial/future use {33}

Biochemical assessment: A blood sample of 20 ml for determination of plasma catecholamines, plasma metabolomics (see details of metabolomics under the section “Data collection and management”), cardiac enzyme release (P-hs-troponin-T and heart fatty-acid binding protein), neuron-specific enolase (NSE), neurofilament light (NF-L), glial fibrillary acidic protein (GFAP), calcium-binding protein S100B (S100B), ubiquitin carboxyterminal hydrolase L1 (UCH-L1), total tau, and cytokines (tumor necrosis factor alpha, interleukins 6 and 10) will be analyzed at ICU arrival and at 24h, at 48h, and at 72h after onset of SAH symptoms; urine catecholamines during first and second 24 h. In addition, a sample of spinal fluid will be collected through EVD at ICU arrival or as soon as it is in place and at 24h, at 48h, and at 72h after onset of SAH symptoms for assessment of metabolomics. P-hsTn-T and P-NSE will be determined by a local university hospital laboratory with standard methods. The samples will be destroyed 10 years after completion of the study. In addition, the patient has a right to require destruction of the samples at any time. In this study, no tissue samples will be collected, and no genetic analysis are conducted.

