## Statistical methods

### Statistical methods for primary and secondary outcomes {20a}

The primary outcome measure is a global fractional anisotropy of white matter of diffusion tensor imaging (DTI) as assessed in the 1st MRI. The univariate distributions of variables and the associations between variables will be described using summary statistics. Basic statistical tests (two-sample *t*-test, Mann-Whitney *U*-test, chi-square test, and Fisher exact test) will be used in the preliminary analysis to compare the xenon-treated and control groups. Kaplan-Meier curves and Cox regression analyses will be applied when examining the occurrence of end-point events. An analysis of variance of repeated measurements will be applied for normally distributed outcome variables. In the case of other types of variables, the analysis will be based on generalized linear mixed models which include comprehensive and general tools to analyze longitudinal data. General linear model for normally distributed outcomes and generalized linear models for other types of variables will be used for analyzing data at different time points. The analyses will be adjusted for age, sex, and site, and other baseline characteristics of patients will be used as covariates when needed. The adjusted analysis will be considered to be the main analysis. The statistical analysis will be based on all available data. If an analysis is based only on complete cases, it will be mentioned separately. The data will be analyzed according to intention-to-treat and per-protocol populations. The differences will be presented as mean differences with 95% confidence intervals for continuous outcomes, odds ratios with 95% confidence intervals for categorical outcomes, and hazard ratios with 95% confidence intervals in survival analyses. A two-sided statistical test with a significance level of 0.05 will be used in the statistical analyses.

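### The ICU-arrival biomarker value, in effect a pre-xenon baseline, has no fixed role in the analysis; naming it as a covariate would sharpen the secondary biomarker comparisons at almost no cost

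*Protocol article*

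**What the plan says.** Three parts of the protocol article bear on this point.

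- **Sampling** (biological specimens, {33}). The blood markers, which include catecholamines, cardiac enzymes, NSE, NF-L, GFAP, S100B, UCH-L1, tau and cytokines, "will be analyzed at ICU arrival and at 24h, at 48h, and at 72h after onset of SAH symptoms". CSF for metabolomics follows the same schedule, except that the first sample may wait until the ventricular drain is in place.
- **Start of xenon** (Intervention description, {11a}). Xenon is given "for 24 h upon admission to the intensive care unit", and "The ICP monitoring device must be in place prior to the commencement of xenon inhalation". The ICU-arrival blood sample is therefore, in effect, taken before xenon can act.
- **Analysis** ({20a}). "An analysis of variance of repeated measurements will be applied for normally distributed outcome variables". Other types of variable go to generalized linear mixed models. General or generalized linear models "will be used for analyzing data at different time points". On covariates: "The analyses will be adjusted for age, sex, and site, and other baseline characteristics of patients will be used as covariates when needed". This adjusted version is the main analysis, and continuous outcomes are reported as mean differences with 95% confidence intervals.

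The section does not say whether the arrival value is a response or a covariate, or which effect in the repeated-measures model (group, or group by time) tests xenon.

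**The concern.** The secondary objectives ask whether xenon changes the release of these markers. Patients will differ widely in initial injury, and the arrival sample measures that difference before treatment. Used as a covariate, it removes between-patient variation from the comparison. Left out, that variation stays in the error term. Entered as a fourth response with the group main effect as the test, it also pulls the estimate towards zero, because randomisation makes the expected difference at arrival nil.

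The article fixes age, sex and site as covariates but leaves what may be the most informative one to a condition (when needed) with no criterion. At stake is precision on the secondary biomarker outcomes, and some avoidable discretion across many markers. A null biomarker result could then reflect the analysis rather than xenon.

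**Working it through.** **The plan's own figure.** No power is stated for any biomarker. The only stated calculation is for the primary endpoint (difference 0.02, SD 0.035, 80% power, two-sided 0.05): 2 × (1.960 + 0.842)² × (0.035/0.02)² = 2 × 7.849 × 3.0625 = 48.1 per arm. The t-based solution is 49.05, so 50 per arm, or 100 in total as stated. It is not affected by this point.

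**Inputs for the biomarker check.**

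- From the article: four sampling times, 80 enrolled per arm, two-sided 0.05.
- Assumed, because the article gives nothing: SD 1 at each time, equal correlation ρ between samples, and the same effect d at 24, 48 and 72 h with zero at arrival.

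**Per-patient variances.**

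- Mean of the three later samples, unadjusted: (1 + 2ρ)/3. At ρ = 0.5 this is 0.667.
- The same mean adjusted for the arrival value: (1 + 2ρ)/3 − ρ². At ρ = 0.5 this is 0.417.
- Mean of all four samples: (1 + 3ρ)/4. At ρ = 0.5 this is 0.625.

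**Effect size.** Set d so that the adjusted analysis has 80% power: d = 2.802 × √(2 × 0.417/80) = 0.286.

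**Power at ρ = 0.5.**

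- Unadjusted 24 to 72 h mean: 0.286/√(2 × 0.667/80) = 2.21; Φ(2.21 − 1.96) ≈ 60%.
- Group main effect over four samples: the average of 0, d, d, d is 0.75d, so 0.75 × 0.286/√(2 × 0.625/80) = 1.72; Φ(1.72 − 1.96) ≈ 40%.
- Group by time (3 df): noncentrality (80/2) × 0.75d²/(1 − ρ) = 4.91; power 43% by the noncentral F distribution, and 44% by simulation.

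So about 20 of the 40 points lost under the main-effect reading come from omitting baseline adjustment (80% to 60%), and about 20 from averaging in the arrival sample (60% to 40%).

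**Separate time points, same d and ρ.** Unadjusted: 0.286/√(2/80) = 1.81, power 44%. Adjusted for arrival, with variance 1 − ρ² = 0.75: 0.286/√(2 × 0.75/80) = 2.09, power 55%. Baseline adjustment helps here too.

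**Range over ρ, with d reset each time so that the adjusted analysis has 80%.**

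| ρ | unadjusted 24–72 h mean | main effect, four samples | group by time |
|---|---|---|---|
| 0.3 | 72% | 53% | 33% |
| 0.5 | 60% | 40% | 43% |
| 0.8 | 30% | 19% | 56% |

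Simulation agrees to within about a point. With serially decaying correlation of 0.5 to 0.8, it gives 55% down to 33% for the main effect and 41% up to 61% for group by time. At a decaying correlation of 0.3 the main effect keeps 63%. If the effect grows over time, group by time can reach about 80% at correlation 0.8.

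**A case where group by time does as well.** Let the effect halve at each step (d, d/2, d/4) with ρ = 0.5 and 80 per arm, and set d so that the unadjusted three-sample mean has 80% power. Both the baseline-adjusted mean and the group-by-time test then have about 94%.

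**Type I error.** Simulated null rejection was 4 to 6%, apart from 7% for the uncorrected group-by-time F-test under a decaying correlation of 0.8. That is a sphericity matter, not a consequence of how the arrival value is used.

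**The case against.** A reader might infer that the repeated-measures ANOVA takes the arrival sample as a response and tests xenon by the four-sample mean, so that the planned test is diluted. The article does not support that. It lists no response times for the ANOVA and names no contrast. Group by time is an equally natural test, in which the arrival sample is the reference rather than a diluent. It also suits an objective worded as release, which the article describes for the earlier cardiac-arrest trial as running from baseline to 72 h. Separate time-point models are planned as well, and these average nothing. The ANOVA sentence covers only normally distributed outcomes, and several markers may be skewed. All of this stands, and the 40% figure therefore belongs to one possible reading.

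It can also be said that "other baseline characteristics of patients will be used as covariates when needed" already permits the arrival value as a covariate, that such detail usually sits in an analysis plan, which is not shown, and that these are secondary outcomes of an exploratory phase II trial. That lowers the weight of the point but does not remove it. The article did choose to fix the main analysis and its named covariates, and the arrival value is left conditional under every planned model. The benefit of adjusting for it does not depend on the dilution reading: it appears for the unadjusted 24 to 72 h mean and at single time points. Against group by time it appears across most of the settings examined, but not all.

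**Conclusion.** The point holds as an inexpensive improvement to the secondary biomarker analyses, not as an error in the plan. The pre-xenon arrival value has no fixed role, and giving it one would raise precision. At ρ = 0.5, with a constant effect and 80 per arm, the comparison is 80% power with baseline adjustment against about 60% without it. The figure is about 40% only if the arrival sample is also averaged in and the group main effect is tested, and about 44% for group by time. Group by time improves at high correlation and with an effect that changes over time.

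The figures rest on assumed correlations and effect profiles and are illustrative. The constant profile is a simplification: the 24 h sample, timed from symptom onset, is taken before a 24 h inhalation begun after onset can have finished. Reading the arrival sample as pre-xenon is an inference from the treatment sequence. It is secure for blood but less so for CSF, where the first sample may be later. Type I error, the primary endpoint and the sample size are not affected.

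**What to change.** In {20a}, add one sentence for serial blood and CSF markers. It should state that:

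- the ICU-arrival value enters as a covariate alongside age, sex and site, on the log scale where skewed;
- only the 24, 48 and 72 h values are responses, in a mixed model with treatment, time and treatment by time;
- the average post-baseline treatment difference with its 95% CI is reported as the xenon effect, with the time-specific differences beside it.

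Where the arrival value is missing, use a constrained baseline in the mixed model. Treat the first CSF sample as a baseline only where its recorded time precedes xenon.

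The cost is one sentence and a little modelling work. The samples are already scheduled, and no visit, assay or patient is added.

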EBI is a major cause of mortality in aSAH patients [9–11]; it is defined as the period within the first 72 h after the ictus and describes the immediate overall brain injury after the aSAH. The initial clinical severity of the aSAH is the most important factor determining the overall outcome; this is assessed by a preliminary assessment of radiographic findings and neurological consciousness using the Glasgow Coma Scale (GCS), together with Hunt-Hess or WFNS grading. Initial radiographic markers of EBI (e.g., cytotoxic edema) are significant predictors of secondary complications and outcomes [9–11]. The pathophysiological disturbances underlying the radiographic findings during the EBI period are not completely understood; however, acute global ischemia, ischemia/reperfusion injury from the transient circulatory arrest at ictus, increased intracranial pressure (ICP), decrease in cerebral blood flow (CBF), and perfusion pressure (CPP) are clinically relevant pathological processes which can result in neuronal death. In addition, other pathophysiological mechanisms during the EBI period include disruptions of the blood-brain barrier, brain swelling, vasogenic and cytotoxic edema, acute vasospasm, dysfunction of autoregulation, altered ionic homeostasis, disruption of vascular integrity, excitotoxicity (e.g., via glutamate-activated receptors), thrombin activation, oxidative stress, inflammation (via activation of microglial cells), increased levels of matrix metalloproteinase (MMP) 9, and activation of the nitric oxide synthase (NOS) pathway. It has been suggested that there may be a causal relationship between delayed cerebral ischemia (DCI) and the severity of EBI. Therefore, an implementation of new treatment modalities targeting EBI seems to represent a promising avenue to attenuate its secondary injuries such as DCI and cerebral infarction [9–11].

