### Trial design {8}

The Xe-SAH study is a prospective, multicenter phase II drug intervention trial. The study design is a single-blind, prospective superiority randomized two-armed parallel follow-up study. The primary objective of the study is to explore the potential neuroprotective effects of xenon, when administered within 6 h of the initial insult, in adult (≥ 18 years of age), mechanically ventilated aSAH patients with a Hunt-Hess grading of 3–5. There are two study arms: the control arm receiving the current standard of care while the intervention arm will be administered a 24-h xenon treatment in addition to the standard care.

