## Assignment of interventions: allocation

### Sequence generation {16a}

After screening, an eligible patient will be included in the study and randomly allocated into either the standard of care arm or the xenon intervention arm in a ratio of 1:1. Informed written consent of participation will be received from the next of kin or the legal representative of the included patient as soon as possible. Trial sites will have access to an Internet-based randomization system. Each subject will be assigned a unique study and randomization number. A block randomization approach will be stratified by the study site.

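### The main adjusted model fixes age, sex and site, leaves other baseline covariates open without a rule, and does not prespecify initial clinical severity

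*Protocol article*

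**What the plan says.** All places are in the protocol article.

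- **Statistical methods for primary and secondary outcomes {20a}.** The endpoint: "The primary outcome measure is a global fractional anisotropy of white matter of diffusion tensor imaging (DTI) as assessed in the 1st MRI". The covariates: "The analyses will be adjusted for age, sex, and site, and other baseline characteristics of patients will be used as covariates when needed". The status of that model: "The adjusted analysis will be considered to be the main analysis". No criterion, time point or decision-maker is given for adding covariates.
- **Background and rationale {6a}.** "The initial clinical severity of the aSAH is the most important factor determining the overall outcome". Severity is assessed from radiographic findings and from the level of consciousness, "using the Glasgow Coma Scale (GCS), together with Hunt-Hess or WFNS grading".
- **Trial design {8} and Eligibility criteria {10}.** Patients must have a "Hunt-Hess grading of 3–5", and the eligibility list also requires a GCS of 3 to 12. Both measures are therefore known for every patient at entry.
- **Sequence generation {16a}.** Patients are "randomly allocated into either the standard of care arm or the xenon intervention arm in a ratio of 1:1". "A block randomization approach will be stratified by the study site". Severity is not a stratification factor.

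**The concern.** The article does more than leave covariates to an analysis plan. It fixes part of the list, leaves the rest open, and declares the result the main analysis. On the protocol's own account, the part it fixes omits the baseline variable that matters most for outcome, while sex is included. Site-only stratification does not secure balance on severity either.

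Two separate things are at stake:

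1. **Power.** A prognostic covariate already collected at entry is not guaranteed a place in the model.
2. **Prespecification.** A main model whose covariates may be added as required, without a rule, does not define one single test at the 0.05 level.

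**Working it through.** **Inputs.** From Sample size {14}: difference 0.02, SD 0.035, two-sided alpha 0.05, power 80%, 100 evaluable patients, about 30% lost from MRI, 80 enrolled per group. The share of variance in fractional anisotropy that severity explains beyond age, sex and site (R²) is not in the document. It is an assumption here, varied from 0.1 to 0.3.

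**1. Reproduce the stated size.** Standardised difference = 0.02 / 0.035 = 0.571. The two-sample t-test needs 49.05 per arm, rounded up to 50, so 100 in total. This matches the plan. Power at 50 per arm is 80.8%.

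**2. Planned evaluable number.** 80 × (1 − 0.30) = 56 per arm. Power there is 85.0%.

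**3. Add a severity term.** Residual SD = 0.035 × √(1 − R²). The t-test power is recomputed with that SD:

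| R² (assumed) | Residual SD | Power, 50 per arm | Power, 56 per arm |
|---|---|---|---|
| 0 | 0.0350 | 80.8% | 85.0% |
| 0.1 | 0.0332 | 84.7% | 88.5% |
| 0.2 | 0.0313 | 88.6% | 91.8% |
| 0.3 | 0.0293 | 92.2% | 94.8% |

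The first row treats 0.035 as the SD left after age, sex and site. One or two degrees of freedom for severity are negligible at this size.

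**4. Cost of an open covariate list.** Simulation under no treatment effect, 50 per arm, with age, sex and site always in the model. K further independent covariates were optional and jointly explained R² = 0.1 or 0.3. All subsets of the optional covariates were fitted. There were 8,000 replicates for K = 1 to 3 and 5,000 for K = 4.

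| Optional covariates K | Type I error if the most favourable subset is reported |
|---|---|
| 1 | 6.0–7.5% |
| 2 | 7.5–9.6% |
| 3 | 7.4–10.8% |
| 4 | 8.7–10.7% |

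The two models fixed in advance, with none or all of the optional covariates, gave 4.0–5.2%. The excess comes from choosing among models, not from leaving any particular covariate out.

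**5. Clinical outcomes.** The same section reports odds ratios and hazard ratios. The background statement on severity applies to these outcomes directly. Such ratios are also non-collapsible: adding a strong prognostic factor changes the quantity being estimated as well as the power. That is a further reason to settle the covariates in advance.

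**The case against.** The strongest defence is that a model with age, sex and site is valid. Under 1:1 randomisation it is unbiased and keeps its type I error, and the confidence interval already allows for chance imbalance in severity. Severity is not excluded either, since it can enter as another baseline characteristic. An analysis plan not shown here may name the covariates before the data are seen. At 56 scanned per arm, power already exceeds 80% without severity. All of this stands. It limits the point to power and prespecification. It does not explain why the article fixes a list without severity and leaves the rest without a rule.

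Four stronger readings are tempting, and the document does not support them:

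- **That omitting severity biases the comparison or inflates alpha.** It does neither. The alpha risk comes only from the open clause.
- **That covariates will be chosen after unblinded data are seen.** The article does not say when or by whom they are chosen. It only fails to rule this out, so 6–11% is a worst case and not a forecast.
- **That severity is the strongest predictor of fractional anisotropy.** The background speaks of overall outcome. No association with fractional anisotropy is given, and restriction to grades 3 to 5 narrows the range and may weaken one.
- **That loss of MRI scans follows severity.** This is plausible, since Strategies to improve adherence {11c} limits imaging to patients who can be scanned safely. It is not stated, and the point does not need it.

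**Conclusion.** The point holds as a matter of power and prespecification, and is worth acting on because it is nearly free. The wording defect is certain: the main model is only partly specified, and severity has no assured place in it by design or by analysis. The size of the power gain for the primary endpoint is conditional. It is roughly 4 to 11 percentage points at 50 per arm and 3 to 10 at 56 per arm if severity adds 10% to 30% of explained variance, and smaller if it adds less. For the clinical outcomes the case rests on the protocol's own statement about severity, and no figure can be put on the gain from the document. The 6–11% type I error assumes one to four optional covariates and selection of the most favourable model.

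**What to change.** State the main model for the primary and clinical outcomes as treatment, site, age, sex and one prespecified severity term with its coding, for example Hunt-Hess grade 3, 4 or 5 at eligibility. Delete the clause admitting further covariates for that model, and label any other adjustment as a sensitivity analysis.

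One severity term is enough, because Hunt-Hess grade and GCS overlap. The fix need not extend to adjusting blood biomarkers for the ICU-arrival value. That would be sound only if the sample is confirmed to precede xenon, which the section on biological specimens {33} does not say.

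The cost is a change of wording and one or two degrees of freedom (one if grade enters as a linear term, two if categorical). The data are already collected at entry and the sample size is unchanged.
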